**Objective:**

The purpose of our pilot study is to examine the efficacy of using a smartphone mobile health (mHealth) app to deliver cognitive behavioral therapy and diminish the severity and prevalence of PICS-F symptoms in family members of critically ill patients.

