### Study Aims

The findings from our pilot study will allow for the collection of preliminary data that are needed for planning a fully powered randomized controlled study. The specific study aims are as follows: (1) determine the prevalence and severity of PICS-F symptoms (anxiety, depression, and posttraumatic stress), health-related quality of life (HRQOL), and MHSE in family decision makers of critically ill patients and their changes over time (at enrollment, 30 days after enrollment, and 60 days after enrollment); (2) determine differences in PICS-F symptom severity, HRQOL, and MHSE between family decision makers (ie, those of critically ill patients) receiving an mHealth app intervention and family members receiving standard care and support; and (3) determine the relationship between the dose of the mHealth app (total time spent with the app and the total number of log-ins) over the course of the study (60 days) and changes in PICS-F symptom severity (anxiety, depression, and posttraumatic stress), HRQOL, and MHSE.

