#### Hospital Anxiety and Depression Scale

Symptoms of anxiety and depression will be assessed by using the 14-item Hospital Anxiety and Depression Scale (HADS) instrument [4,17,56,57]. The HADS is a 14-item scale with 7 items that form an anxiety subscale (HADS-A) and 7 items that form a depression subscale (HADS-D). Each of the two subscales can have scores that range from 0 to 21. Higher scores indicate higher levels of anxiety or depression symptoms. A cutoff score of ≥11 is consistent with moderate-to-severe symptoms of anxiety or depression.

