#### PTSD Checklist for the Diagnostic and Statistical Manual of Mental Disorders, Fifth Edition

Symptoms of posttraumatic stress will be measured by using the 20-item PTSD Checklist for the *Diagnostic and Statistical Manual of Mental Disorders, Fifth Edition* (PCL-5) instrument [58]. The PCL-5 is a 20-item self-report measure that corresponds to the *Diagnostic and Statistical Manual of Mental Disorders,*
*Fifth Edition* criteria for PTSD [59]. A total symptom severity score (range 0-80) can be obtained by summing all of the items’ scores. Higher scores indicate a higher severity of PTSD symptoms. A cutoff score of 31 or higher is the recommended indicator for a provisional diagnosis of PTSD.

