### Data Analysis and Statistical Plan

Data will be analyzed by using SPSS, version 25 (IBM Corporation), and descriptive statistics will be used to assess the frequencies and variability of the data, coding inaccuracies, outliers, and missing data. The statistical plan for each specific aim is detailed in the following subsections.

#### Aim 1

We will report study variables with descriptive statistics. Changes over time will be examined with a repeated-measures analysis of variance.

#### Aim 2

Differences between the intervention and control groups will be assessed with a two-tailed Student *t* test. Differences between groups with regard to the severity of PICS-F symptoms will be used to calculate the effect size for the intervention.

#### Aim 3

The relationship between total mHealth app doses and longitudinal changes in study variables will be examined with a Pearson correlation analysis.

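### Aim 2 promises one effect size for the intervention, but up to six PICS-F comparisons could supply it and none is fixed as primary, so the choice can follow the data

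*Protocol article*

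**What the plan says.** The Objective in the Abstract is worded as efficacy: "The purpose of our pilot study is to examine the efficacy of using a smartphone mobile health (mHealth) app". Study Aims, aim 2, is to "determine differences in PICS-F symptom severity, HRQOL, and MHSE between family decision makers" in the two arms. The Aim 2 analysis in Data Analysis and Statistical Plan is a two-sided Student t test between arms, followed by: "Differences between groups with regard to the severity of PICS-F symptoms will be used to calculate the effect size for the intervention". The effect size is in the singular and is tied to PICS-F severity.

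The Instruments section gives two HADS subscale scores, one PCL-5 total, one MHSE total, and physical and mental SF-12 summaries. Table 1 shows HADS, PCL-5 and MHSE at T1, T2 and T3, and SF-12 at T1 and T3 only. The Abstract's Conclusions and Study Aims both say the results will be used to plan a larger, adequately powered trial. No section names a primary outcome, a primary visit or the visit at which the t test is done, and no alpha is stated.

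**The concern.** The plan commits to one effect size, but its own measurements yield several and it gives no basis for preferring one. If that choice is left until the results are known, it can be influenced by them.

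Two things are at stake:

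- **The planning value.** An effect picked because it looks best overstates the truth, and a main trial sized on it would be too small.
- **The efficacy reading.** With several t tests and no designated contrast, one nominally significant result could be presented as the answer to the stated purpose.

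**Working it through.** **Plan's own figure.** Sample and Setting gives 60 participants, 30 per arm, from a cited pilot-size recommendation for a small effect, with 30% attrition. The article gives no numerical effect, alpha or power, so 60 cannot be reproduced. What follows from it is 30 × 0.7 = 21 completers per arm.

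**Count of comparisons (Instruments and Table 1).**
- Candidates for the effect size: 3 PICS-F scores × 2 visits = 6, or 3 if only T3 is tested.
- All Aim 2 comparisons: (HADS-A, HADS-D, PCL-5, MHSE) × 2 visits + 2 SF-12 scores at T3 = 8 + 2 = 10, or 6 if only T3 is tested.

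**Chance of at least one p < 0.05 with no true effect (alpha of 0.05 assumed).** If the tests were independent:
- ten tests: 1 − 0.95^10 = 40.1%; favouring the app only, 1 − 0.975^10 = 22.4%
- six tests: 1 − 0.95^6 = 26.5%; favouring the app only, 1 − 0.975^6 = 14.1%
- three tests: 1 − 0.95^3 = 14.3%

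Subscales and repeat visits in the same people are correlated, so independence is the upper end. The article gives no correlations. The table shows assumed values, from 8,000 simulated trials per row with 21 per arm and no true effect.

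| Correlation between scores, between visits | At least 1 of 10, two-sided | At least 1 of 10, favouring app | At least 1 of 6, two-sided | Mean largest of 6 effects (SD) |
|---|---|---|---|---|
| 0, 0 | 40.4% | 23.1% | 26.9% | 0.40 |
| 0.3, 0.5 | 35.6% | 18.8% | 23.8% | 0.34 |
| 0.5, 0.6 | 30.6% | 15.2% | 21.2% | 0.29 |
| 0.7, 0.7 | 23.6% | 12.3% | 17.5% | 0.24 |
| 0.8, 0.8 | 18.9% | 9.2% | 14.7% | 0.20 |

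The first row agrees with the exact figures to within simulation error.

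**Largest effect, checked by formula.** The standard error of a standardised difference near zero is √(2/21) = 0.309. The expected maximum of six standard normals with common correlation ρ is 1.267 × √(1 − ρ). This gives:
- ρ = 0: 1.267 × 0.309 = 0.39
- ρ = 0.5: 0.896 × 0.309 = 0.28
- ρ = 0.7: 0.694 × 0.309 = 0.21

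For the three T3 scores alone, the simulated mean maximum is 0.12 to 0.27 SD.

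**What selection would do to the next trial.** Take a true effect of 0.2 SD on every scale (an assumption for small). At 21 per arm, the largest of six then averages 0.41 to 0.54 SD over the correlated rows, at least double the truth. By the normal approximation at 80% power, n per arm = 2 × 2.80² / d²:
- d = 0.2 needs about 393
- d = 0.41 gives about 94
- d = 0.54 gives about 54

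With 54 to 94 per arm, power at a true 0.2 is only about 18% to 28%. This applies only if the largest effect is the one carried forward.

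**The case against.** Several counter-arguments have force.

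- **Selection is not stated.** A reader might infer that the best-looking effect will be used and will be inflated. The article does not say so. Reporting one effect size per symptom is also consistent with its wording and selects nothing. This stands: the inflation figures are conditional. What remains is that the text leaves the choice open.
- **The effect size does not have ten candidates.** The Aim 2 sentence limits it to PICS-F severity, which excludes MHSE and SF-12. This stands: the number is six at most, and ten applies only to the wider set of efficacy comparisons. Both counts are themselves upper limits, because no visit is given for the t test and Table 1 shows when data are collected, not when arms are compared.
- **A false positive is not likely.** A reader might infer that a chance finding is to be expected. Even under independence the figure is about 40%, and an efficacy claim needs a result in the app's favour, at about 9% to 22%. This stands: the risk is well above the nominal level but not more likely than not.
- **This is a pilot, and a SAP may exist.** A pilot need not control family-wise error, and multiplicity rules commonly sit in a SAP. That is accepted, and no such rule is asked for here. But which outcome and visit carry the main question is a protocol-level choice. The article says that its subsections detail the plan for each aim, and its purpose is worded as efficacy.
- **Baseline adjustment is a separate matter.** It is not needed to cure the selection problem. It is included in the fix because the chosen contrast has to be estimated somehow and T1 scores are already collected before randomisation.

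**Conclusion.** The point holds in a limited form. The article promises a single effect size that its design does not identify: up to six PICS-F comparisons qualify (three if only T3 is tested), within up to ten unadjusted t tests, and none is primary. The choice can therefore follow the data.

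The risk of at least one two-sided false positive in ten tests is about 20% to 40%. If the largest of six effects were chosen, it would average about 0.2 to 0.4 SD under no true effect. These sizes rest on an alpha of 0.05, the correlations tabulated above, 21 completers per arm and, for the ten-test and six-effect figures, comparisons at both follow-up visits. None of this shows that the sponsor intends to select a favourable result. The matter should be settled before the analysis.

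**What to change.** Add to the Aim 2 analysis, before any outcome data are analysed by arm:

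- Name one PICS-F scale at T3 as the primary contrast. T3 matches the 60-day period over which app use is measured.
- Estimate that contrast by ANCOVA with the T1 score as covariate, in place of the unadjusted t test.
- State that the effect size used to plan the next trial, with its 95% CI, comes from that contrast only. The interval matters: at 21 per arm its unadjusted half-width is about 1.96 × 0.309 = 0.61 SD.
- Report the remaining comparisons (up to nine) as supportive estimates with 95% CIs, and do not read them as evidence of efficacy.

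This takes a few lines and no new data, since T1 and T3 scores are already scheduled. The sponsor gives up choosing the scale or visit after seeing the results, and one scale will stand for a syndrome with several symptoms. The supportive estimates keep the other symptoms in view.

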### Human Subjects and Ethical Issues

The study will undergo review and approval by the institutional review board at Summa Health. The investigators have considerable experience in conducting research on individuals with symptoms of anxiety, depression, and posttraumatic stress. The study will present no more than minimal psychological risk and harm, which largely come from the possibility that answering the questions on the anxiety, depression, and stress instruments may be distressing for participants. Psychological risk will be minimized by emphasizing that study participants can stop participating in the study at any time and are not obligated to answer any question that they find to be distressing. Family members who exhibit clinically significant symptoms will be referred to their primary care physician. Family members of patients who die during the study will be referred to local bereavement support groups.

There will be a low risk of privacy or confidentiality loss. This risk will be minimized via the following measures: (1) the only record linking participants and the research data will be the consent document; (2) consent documents will be kept in a locked cabinet in the locked office of the principal investigator; (3) data will be entered and stored by the research assistant on REDCap (Research Electronic Data Capture; Vanderbilt University)—a secure, Health Insurance Portability and Accountability Act–compliant, web-based platform; (4) all data files obtained for analysis will be stored on a password-protected laptop computer, which will be stored in a locked room; and (5) the principal investigator, coinvestigators, and research assistant are the only individuals who will have access to the data files.

## Results

Recruitment for our pilot study began in August 2020. During recruitment, challenges arose due to the COVID-19 pandemic. There was a short period of time when research studies at Summa were placed on hiatus due to COVID-19–related restrictions. This was followed by challenges in recruiting family members while limitations were placed on family visitation to the hospital. Despite these challenges, data collection and analysis are expected to be completed by March 2022. The dissemination of our findings will be accomplished through conferences and publications.

## Discussion

The use of a self-care mHealth app represents a novel approach to addressing the needs and untoward psychological symptoms experienced by family members of critically ill patients by leveraging technology and the growing market penetrance of smartphone ownership. The proposed study emphasizes self-care, which can function as an adjunct and complement to existing nursing efforts for supporting family members of critically ill patients without significantly increasing the need for care delivery resources. Importantly, the proposed mHealth app offers a portable, “just-in-time” benefit to users by being available to them on demand via their smartphone across transitions of care. The findings of our study will inform the planning and implementation of a randomized controlled trial. Additionally, the findings may help to direct collaborations with app developers for modifying existing apps or creating new apps that emphasize self-care specifically for family members and caregivers of acutely and chronically ill patients.

## Appendix

Multimedia Appendix 1 Peer review report from the American Association of Critical-Care Nurses.

## Abbreviations

CBT: cognitive behavioral therapy
HADS: Hospital Anxiety and Depression Scale
HRQOL: health-related quality of life
ICU: intensive care unit
mHealth: mobile health
MHSE: mental health self-efficacy
PCL-5: Posttraumatic Stress Disorder Checklist for the Diagnostic and Statistical Manual of Mental Disorders, Fifth Edition
PICS-F: postintensive care syndrome-family
PTSD: posttraumatic stress disorder
REDCap: Research Electronic Data Capture
